## Abstract

**Background:**

The nutrigenomics, overweight/obesity and weight management trial (NOW Trial) is a pragmatic randomized controlled trial of community-dwelling adults recruited from the Group Lifestyle Balance™ (GLB™) Program. The GLB™ Program (formerly referred to as the Diabetes Prevention Program) is an evidence-based, intensive weight management program, which was offered to overweight/obese patients (BMI ≥ 25.0 kg/m^2^) in a rural Ontario community.

**Methods:**

Patients enrolled in the GLB™ Program were invited to participate in this study. GLB™ groups were randomized 1:1 to receive either the standard GLB™ program + population-based lifestyle advice for weight management, or a modified GLB™ program + personalized, genetic-based lifestyle advice for weight management. The purpose of this study is to determine if the provision of genetic-based lifestyle guidelines is superior to the provision of population-based guidelines in a pragmatic clinical setting to promote changes in: body composition, weight, body mass index, dietary and physical activity habits, as well as attitudes, subjective norms, and behavioural control. The 12-month intervention protocol consists of 23 group-based sessions and 4 one-on-one sessions. Data collection time points include baseline in addition to 3, 6, and 12-month follow up. The comprehensive study design is described in the present manuscript, using both the extended CONSORT checklist for reporting pragmatic trials and the SPIRIT checklist as guidance during manuscript development.

**Discussion:**

Overall, this study seeks to pragmatically determine if the provision of DNA-based lifestyle advice leads to improved health and lifestyle outcomes compared to the provision of standard, population-based lifestyle advice. The results of this trial can be used to inform clinical and community nutrition practice guidelines.

**Trial registration:**

This study was registered with clinicaltrials.gov: NCT03015012 on January 9, 2017.

**Electronic supplementary material:**

The online version of this article (10.1186/s12889-019-6621-8) contains supplementary material, which is available to authorized users.

## Background

Lifestyle modification of nutrition and physical activity are often recommended to help manage overweight and obesity [1]. Despite increased knowledge of beneficial lifestyle strategies for weight management, rates of overweight and obesity continue to climb among adults in Canada and the United States [2, 3]. The Group Lifestyle Balance™ (GLB™) program is one of the most successful lifestyle-based weight management programs and is currently offered in over 80 primary care settings in the United States and is now becoming increasingly prevalent in Canada [4]. The GLB™ program was originally intended only for individuals with prediabetes and was formerly referred to as The Diabetes Prevention Program (DPP). In patients with prediabetes, the DPP lifestyle intervention reduced the risk of progressing to type 2 diabetes by 58%, while the biguanide antihyperglycemic agent, Metformin, reduced the risk of type 2 diabetes by 31% when compared to a placebo pill [5]. Given the documented success of the DPP, the Ontario Ministry of Health and Long-Term Care encouraged program expansion through broader eligibility criteria [6], and as such some clinics are now offering this program for general weight management (regardless of receiving a prediabetes diagnosis), since overweight and obesity are considered risk factors for the development of type 2 diabetes [7].

Although the GLB™ program has proven to be successful [5, 8, 9], a “one-size fits all” approach to weight management has been critiqued by experts, who argue that this generalized approach yields minimal weight loss outcomes that do not satisfy the wants and needs of clinicians, researchers and patients alike [10]. Genetic testing is an innovative tool, which has the potential to facilitate positive lifestyle changes and enhance patient outcomes, though this has been widely debated in the literature in recent years [11–14]. A systematic review found that actionable lifestyle recommendations (e.g., “reduce your consumption of sodium”) facilitated behaviour change greater than the provision of simple genetic-based disease-risk estimates, and that nutrition was the most promising lifestyle habit that could be motivated by lifestyle genomics testing [11].

A few studies have assessed change in weight from the provision of genetic-based information compared to a standard intervention [15–17]. Two studies reported that genetic testing was superior to a standard intervention for changes in weight or BMI [15, 17], and one study showed that adherence to a genetic-based diet was correlated with greater weight loss, whereas adherence to a standard diet was not [16].

There have been considerable scientific advancements in knowledge pertaining to nutrition and physical activity recommendations, which can be personalized based on an individual’s genetic variation. Nutrigenomics is a science that explores the interaction between nutrition, genetics, and health outcomes [18]. The science exploring how nutrition and physical activity, alongside other lifestyle components, can impact health outcomes can be referred to as *lifestyle genomics* [11]. Single nucleotide polymorphisms (SNPs) located within the genes FTO, MC4R, TCF7L2, UCP1, APOA2, and PPARg2 can impact physical activity and dietary approaches to weight management and/or nutritional habits [19–27]. Furthermore, SNPs located within the genes ACTN3, NFIA-AS2, ADRB3, NRF2 and GSTP1 have been shown to impact genetic predisposition to excel in either endurance or strength-based activities [28–32]. These genetic variants were used in the genetic test provided in the present study as they are currently offered through commercial genetic testing [33], thus optimizing the pragmatic nature of this trial.

While genetics certainly plays a role in obesity, there are multiple factors contributing to the current obesity epidemic, including diminished energy expenditure, increased energy intake, rising food costs, the built environment, socioeconomic status, and other social determinants of health [34–39]. Several of these factors can be modified such as energy intake and energy expenditure.

The Theory of Planned Behaviour (TPB) posits that attitudes towards a behaviour, subjective norms, perceived behavioural control and actual behavioural control can be used to predict intentions and behaviours [40]. Although the TPB is one of the most widely-accepted behaviour change theories, it has yet to be incorporated into genetic testing behaviour change research [11, 41] despite a recent call to incorporate this theory into personalized healthcare behaviour change research [41]. By considering this theory, we can account for many contributors impacting behaviour change and therefore account for several confounding factors, which could influence study results. The present randomized controlled trial is the first study to intentionally incorporate the TPB into genetic testing behaviour change research.

The proposed extended CONSORT checklist for reporting pragmatic trials [42] was used to guide the development of the current manuscript. The complete checklist can be reviewed in Additional file 1, with items 1 through 16 being relevant for purposes of this paper.

## Methods/design

### Objectives

The primary objective of this study is to determine if the provision of genetic-based lifestyle advice reduces body fat percentage to a greater extent than the provision of population-based lifestyle advice. Secondary objectives include determining whether the provision of genetic-based lifestyle advice (a) helps to motivate healthful changes to dietary intake and physical activity, (b) leads to greater improvements in anthropometric measures such as weight, BMI, lean mass, fat mass (kg), and water weight, and (c) influences attitudes, subjective norms, behavioural control, and intention to make lifestyle changes. The tertiary objective is to determine if there is a nutrigenomics interaction between ACE rs4343 genetic variation, sodium and water intake, and water weight.

### Hypotheses

Compared to the provision of population-based lifestyle advice, providing DNA-based lifestyle advice will lead to significantly greater improvements in: body fat percentage, attitudes and intentions towards behaviour change, the adoption of healthier dietary and physical activity habits, as well as improved weight, and BMI. Furthermore, we hypothesize that ACE rs4343 genetic variation will lead to increased water weight when sodium intake is high.

### Material and methods

The flow of the study protocol for this parallel group, superiority randomized controlled trial is outlined in Figs. 1, 2 and 3. Further details are provided below.

**Fig. 1 Fig1:**
[figure not shown]
Flow of Study Protocol

**Fig. 2 Fig2:**
[figure not shown]
CONSORT 2010 Flow Diagram (Clinical Trial Registration Number: NCT03015012)

**Fig. 3 Fig3:**
[figure not shown]
SPIRIT Flow Diagram of The NOW Trial Study Protocol at the EEFHT. SE: study entry; Mo: month

#### Sample size calculation

Seventy-four participants (*n* = 37 per group) are needed in this study to detect a clinically meaningful difference of 4% in body fat percentage, assuming 80% power, an alpha of 5%, and a standard deviation of 6.1% [43]. We aimed to recruit 88 participants (*n* = 44 per group) to account for the potential dropout rate of 20%. While minimal research exists outlining a clinically meaningful change in body fat percentage, a 5% change in weight (which would come from fat mass, water weight and/or muscle mass) is often reported to be clinically meaningful [44]. Furthermore, clinical experience from the registered dietitians involved in this study helped to determine the clinically meaningful 4% difference mentioned above. This difference has also been supported in published reference standards of body fat percentage in Caucasian adults which indicate that a 4% change in body fat percentage is associated with a 1 – 2 decile change on the reference standards charts [45].

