#### Cohort randomization

A cohort randomization model was used rather than subject randomization to allow all participants in a given GLB™ group to obtain the same intervention. At the time of randomization, 12 cohorts (GLB™ groups) were randomized 1:1 to either the personalized lifestyle intervention (PLI) based on genetics, or the standard lifestyle intervention (SLI) based on population-based guidelines. It was anticipated that 12 groups of approximately 7 participants each would be needed to obtain the desired sample size of 88 participants. Prior to obtaining informed consent from participants, randomly permuted blocks were generated using the original generator on an internet-based randomization program [46]. Since participant recruitment was quicker than anticipated and there was an even 1:1 split of a PLI and a SLI group in the last two randomized groups, only 10 of the randomized groups (5 PLI groups, 5 SLI groups) were used, resulting in a total of *N* = 140 participants in the study (mean number of study participants per group ± SD = 14.0 ± 4.1).

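### The stated 80% power comes from a formula for individually randomised participants, although whole GLB groups were randomised; whether the 10 groups used still give 80% depends on an ICC that the article does not state

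*Protocol article*

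**What the plan says.** Protocol article, Sample size calculation: the requirement is 74 analysed, 37 in each arm. The aim is worded as "to detect a clinically meaningful difference of 4% in body fat percentage". The other inputs follow in the same sentence: "assuming 80% power, an alpha of 5%, and a standard deviation of 6.1" (in percentage points). The target is then raised to 88 (44 per arm), and the only reason given is "to account for the potential dropout rate of 20"%. The section mentions no ICC, design effect or number of groups.

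Protocol article, Cohort randomization: "A cohort randomization model was used rather than subject randomization". It states that "12 cohorts (GLB™ groups) were randomized 1:1", and explains the number of groups from the head count alone: "It was anticipated that 12 groups of approximately 7 participants each would be needed to obtain the desired sample size of 88 participants". Recruitment ran faster than expected, so "only 10 of the randomized groups (5 PLI groups, 5 SLI groups) were used", with 140 participants and a mean group size of 14.0 (SD 4.1). No revised power appears in the article.

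**The concern.** The two sections describe different designs. The sample size treats each participant as an independent unit. The randomisation section makes the GLB group the unit.

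Members of one group share the group sessions, the season and the time of day, and they chose the group that suited their availability (Staggered cohorts; Interventions). Some correlation of outcomes within groups is therefore plausible. With few groups per arm, the treatment comparison also has few between-group degrees of freedom. Both reduce power relative to the stated figure.

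Body fat percentage is the primary outcome. If the stated 80% is taken at face value, a null result would be read as stronger evidence against a 4-point effect than the design may provide.

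**Working it through.** **Inputs from the article.** Difference 4 points, SD 6.1, power 80%, alpha 5%, 74 analysed (Sample size calculation). 12 groups planned; 10 used, N = 140, mean size 14.0, SD 4.1 (Cohort randomization). Dropout 20% (Sample size calculation).

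**Assumed.** ICC 0.01 to 0.10, because none is stated. Two-sided test. SD 6.1 applies to the outcome analysed. Planned groups of equal size. The relative spread of group sizes is unchanged by dropout.

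**Step 1: reproduce the stated size.** n per arm = 2 × (1.96 + 0.84)² × (6.1/4)² = 36.5, rounded up to 37, so 74 in total. The formula for independent participants gives the stated figure exactly, which leaves no room for a design effect.

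**Step 2: allow for groups.**
- Design effect: DE = 1 + ((1 + CV²) × m − 1) × ICC, where m is the mean number analysed per group and CV is the SD of group size divided by its mean.
- Standard error of the difference: SE = 6.1 × √(4 × DE / N).
- Power: noncentral t with (number of groups − 2) df and noncentrality 4/SE. The normal reference is shown beside it.

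**Step 3: planned 12 groups, 74 analysed** (m = 74/12 = 6.17, CV taken as 0, 10 df)

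| ICC | DE | Power, t on 10 df | Power, normal |
|---|---|---|---|
| 0 | 1.00 | 72% | 81% |
| 0.02 | 1.10 | 68% | 77% |
| 0.05 | 1.26 | 62% | 71% |
| 0.10 | 1.52 | 54% | 63% |

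The drop from 81% to 72% at ICC 0 comes from the degrees of freedom, not from correlation. If all 88 were retained, the t-based figures are 79%, 74%, 68% and 58% at ICC 0, 0.02, 0.05 and 0.10.

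**Step 4: the 10 groups used, 20% lost** (N = 112, m = 11.2, CV = 4.1/14 = 0.29, 8 df)

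Example at ICC 0.05: DE = 1 + (1.086 × 11.2 − 1) × 0.05 = 1.56; SE = 6.1 × √(4 × 1.558/112) = 1.44; 4/1.44 = 2.78; power 68%.

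| ICC | DE | Power, t on 8 df | Power, normal | Detectable difference at 80% (t) |
|---|---|---|---|---|
| 0.01 | 1.11 | 82% | 91% | 3.9 |
| 0.02 | 1.22 | 78% | 88% | 4.1 |
| 0.05 | 1.56 | 68% | 79% | 4.6 |
| 0.10 | 2.12 | 55% | 67% | 5.4 |

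With no loss (N = 140), the t-based figures are 89%, 85%, 74% and 59%, and the normal ones 95%, 93%, 84% and 70%.

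**Step 5: largest ICC at which the 10 groups keep 80% power**

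| | t on 8 df | Normal |
|---|---|---|
| 20% lost | 0.016 | 0.048 |
| No loss | 0.033 | 0.065 |

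**The case against.** **Enrolment of 140 helped.** A reader might infer that moving to fewer, larger groups damaged power, since it raises the design effect and cuts the df from 10 to 8. The figures do not support that. Over ICC 0.02, 0.05 and 0.10, power rose from 68%, 62% and 54% under the plan to 78%, 68% and 55% as run with 20% loss. The gain is small at the top of the range, but there is no loss. This objection stands.

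**The ICC may be small.** All sessions were at one site, and the same dietitian led the group and one-on-one sessions, so variation between sites or coaches is absent. Shared group dynamics and self-selected sessions can still produce correlation. The objection limits how large the shortfall can be said to be. It does not justify a calculation that assumes independence.

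**The reference distribution matters.** The t reference is the defensible choice with 10 groups, but the normal one gives about 9 to 12 points more power at the ICCs shown. Both are given above for that reason.

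**The SD may be too large.** The primary outcome is a change, and the article does not say whether 6.1 is an SD of change or of values at one time. As an illustration only, SD 5.0 would give 92%, 84% and 72% at ICC 0.02, 0.05 and 0.10 (10 groups, 20% loss, t on 8 df). This stands as a caveat on every power figure here.

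**Planned power does not bias the result.** This is true: a confidence interval that respects the groups can be read without it. That makes this a correction to a stated figure, not a threat to the estimate.

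**Conclusion.** The point holds in a conditional form. The mismatch between formula and design is certain and does not depend on the ICC: 37 per arm carries no allowance for randomising groups. The size of the consequence is conditional. On between-group df, the 12-group plan with 74 analysed is below 80% at every ICC, partly from the df alone. The 10 groups used keep 80% up to an ICC of about 0.016 with 20% loss and about 0.033 with none, or about 0.048 and 0.065 with a normal reference. Beyond that, power falls to 55% at ICC 0.10 (20% loss, t on 8 df).

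Two stronger readings are tempting but not supported. One is that the trial as run simply lacks 80% power: at a low ICC, or with a smaller SD, it has it. The other is that power was never recalculated: this is a condensed article, and all that can be said is that it reports no revised power.

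The conclusion rests on SD 6.1 applying to the outcome analysed, an assumed ICC range, and an analysis that respects GLB groups. Baseline adjustment could raise power.

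**What to change.** Rewrite the sample-size paragraph, in the protocol or the analysis plan, for the design actually run:

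- State that the 74 came from a calculation for independent participants.
- Give the design parameters: 10 groups, mean size 14, CV 0.29, 20% dropout, 8 between-group df.
- State an ICC range with its justification. Replace the single 80% with power and detectable difference over that range. On the present inputs the detectable difference is 4.1, 4.6 and 5.4 points at ICC 0.02, 0.05 and 0.10.
- Say whether 6.1 is an SD of change, and recompute if it is not the SD of the outcome analysed.
- Report the observed ICC with the results.

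The cost is wording only. No extra participants and no change in conduct are needed. The one drawback is a less favourable stated power.

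### The recruitment target of 88 does not cover the stated 20% dropout: it leaves about 70 participants against a stated requirement of 74, and covers a loss of only about 16%

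*Protocol article*

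**What the plan says.** The section Sample size calculation sets the requirement first: "Seventy-four participants (*n* = 37 per group) are needed in this study". The effect to be found is 4 percentage points of body fat, and the remaining inputs are introduced as "assuming 80% power, an alpha of 5%, and a standard deviation of 6.1" percent. The next sentence gives the recruitment target, "We aimed to recruit 88 participants (*n* = 44 per group"), and its purpose: "to account for the potential dropout rate of 20" percent.

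The section Cohort randomization carries the 88 forward as the desired sample size. It then reports that recruitment ran faster than expected and that 10 of the 12 randomized groups were used, "resulting in a total of *N* = 140 participants in the study". The section Recruitment dates recruitment from April 2017 to September 2018, so the target describes past planning.

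**The concern.** A dropout allowance should leave the required number in the analysis once the assumed share of those enrolled has been lost. Here the requirement, the target and the dropout rate stand in two consecutive sentences, and the third applied to the second does not return the first. No other section of the article reconciles them.

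What is at stake is the accuracy of the published justification. If recruitment had stopped at 88 and dropout had reached 20%, the trial would have fallen short of its own requirement and slightly short of its stated power. The 88 is also the figure against which a reader will judge the actual enrolment.

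**Working it through.** **Inputs**, all from Sample size calculation unless noted: difference 4 percentage points; SD 6.1; power 80%; alpha 5%; requirement 74 (37 per group); target 88 (44 per group); dropout 20%. Enrolment of 140 is from Cohort randomization. The article does not say whether alpha is one- or two-sided. Two-sided is assumed because it reproduces the stated requirement.

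**Step 1: reproduce the requirement.** Normal formula for two means:

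n per group = 2 × (1.960 + 0.842)² × 6.1² / 4² = 36.5, rounded up to 37, so 74 in total.

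This matches the article. (A t-test solution gives 37.5, so 38 per group; the difference is immaterial.)

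**Step 2: apply the stated dropout to the stated target.**

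- 88 × (1 − 0.20) = 70.4 in total
- 44 × 0.80 = 35.2 per group

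This is 3.6 participants below 74.

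**Step 3: what 20% dropout would have needed.**

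- 74 / (1 − 0.20) = 92.5, so 93
- By group: 37 / 0.80 = 46.25, so 47 per group and 94 in total

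The target is 5 to 6 participants short.

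**Step 4: where 88 probably comes from.**

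- 37 × (1 + 0.20) = 44.4 per group, cut to 44, giving 88
- In total: 74 × 1.2 = 88.8

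The figure fits n × (1 + d) where n / (1 − d) was needed.

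**Step 5: the dropout that 88 does cover.**

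1 − 74/88 = 15.9%.

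**Step 6: effect on power, individual level.**

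| Per group | Normal formula | t-test |
|---|---|---|
| 37 | 80.5% | 79.5% |
| 35 | 78.3% | 77.2% |

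Compared within one method, the loss is about 2 percentage points.

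**Step 7: actual enrolment.**

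- 140 × 0.80 = 112, above 74
- 140 would tolerate a loss of 1 − 74/140 = 47.1% before falling below 74

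Both figures count participants and make no allowance for clustering.

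**The case against.** The strongest defence is that nothing in the trial turns on this. Enrolment of 140 exceeds 88, 93 and 94 alike. The 35 per group is also a worst case: the section Statistical analysis plan calls for intention-to-treat mixed models, follow-up is at 3, 6 and 12 months, and the section Follow-up data collection invites everyone regardless of compliance. Someone lost late may still contribute data. All of this stands and keeps the point small. It does not make the sentence correct. Nor does reading the 20% as a simple add-on rescue it, because a dropout rate applies to those enrolled.

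Two stronger readings are tempting, and the article does not support them.

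- *A second error in the group plan.* A reader might multiply 12 by 7, get 84, and conclude that the groups could not reach 88. The article says "12 groups of approximately 7 participants each would be needed to obtain the desired sample size of 88 participants". Since 88/12 = 7.33, the word approximately covers it; 84 appears only if 7 is treated as exact.
- *The target should be rewritten as 94.* Recruitment had ended by September 2018. Replacing 88 with 94, or changing the planned group size to match, would report an aim the trial never had.

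**Conclusion.** The stated target does not deliver the stated requirement at the stated dropout rate. The allowance is 5 to 6 participants short, 88 covers about 16% dropout, and the cost at the planned size would have been about 2 points of power. This rests on the article's own inputs, a two-sided 5% test, the normal formula that reproduces 37 per group, and dropouts contributing nothing to the analysis.

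Severity is minor: a figure wrong as written, with little practical effect because 112 of the 140 would remain after a 20% loss.

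A reader might infer that the trial is underpowered because of this slip; the enrolment figure rules that out at participant level. A reader might equally infer that 140 settles the power question. That does not follow either, because "12 cohorts (GLB™ groups) were randomized 1:1" and the section Sample size calculation states no allowance for clustering. Clustering is a separate matter, and this point does not depend on it.

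**What to change.** Amend the dropout sentence in Sample size calculation, or report the correction with the results:

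- Keep 88 (44 per group) as the recruitment target that was actually set.
- State that it covers a dropout of about 16%, and that 20% would have needed 93 participants, or 94 with equal arms.
- Add that the 140 enrolled leave about 112 after a 20% loss, which exceeds 74 at participant level, before any allowance for clustering.

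Leave the description of the planned groups as it is. The cost is wording only: no data, conduct or analysis changes.
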